### 2.7. Outcomes

Cardiac function indexes: left ventricular end-diastolic diameter, left ventricular end-systolic diameter and left ventricular ejection fraction will be measured by color doppler ultrasonic diagnostic apparatus (GE-VIVID7, US).Blood lipid levels: Fasting veins of the patients will be collected in the morning before and after treatment and during follow-up, and blood lipid index, including total cholesterol; triacylglycerol; low-density lipoprotein cholesterol and high-density lipoprotein cholesterol, were measured by an automatic biochemical analyzer (HITEC-7100, Japan).Number of angina attacks per week, total amount of nitroglycerin tablets taken during the study.

We will collect the above outcome measures at baseline, at the end of treatment, and at the 6th, 12th and 24th week of follow-up.

### 2.8. Safety evaluation

Safety evaluation includes vital signs, blood, urine, and stool routine tests, liver and kidney function, bleeding spots, skin ecchymosis, and adverse events. Any discomfort experienced by the patient during the study will be reported to the investigator, and details of all adverse events will be recorded in the CRF. Safety assessors will assess the safety of both options at the end of the study.

### 2.9. Data management and quality control

Trained researchers will collect research data throughout the study and record in the CRF. Any amendment to the study protocol will be applied in advance and approved by the Ethics Committee of our hospital. To ensure the reliability and confidentiality of the study data. All data will be stored in an independent storage room. Access to the database will be restricted to researchers on this study team. Participants’ information will not be made publicly available and shared without written permission from participants.

### 2.10. Statistical analysis

Outcome measure data will be statistically analyzed by the full analysis set and per-protocol set. Safety evaluation data will be based on safety set. Statistical evaluation of full analysis set will follow intent-to-treat. Data from this study will be statistically analyzed using SPSS22.0 (IBM Company, New York, NY) software. Count and grade data will be expressed as percentage (%), 2-test or non-parametric test; measurement data will be expressed as mean ± standard deviation or interquartile range M (P25, P75), normal distribution will be analyzed by *t*-test, and skewed distribution will be analyzed by non-parametric test; If the data at multiple time points are normal and have homogeneous variance, the analysis of variance will be used, otherwise the generalized estimating equation will be used; The difference will be considered statistically significant when *P <* .05.

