### 2.3. Sample size

The estimation of sample size is based on the mean and standard deviation of the scores of the left ventricular ejection fraction of patients after 12 weeks of treatment. Referring to the results of the preliminary experiment, 54.74 ± 11.17 in the treatment group and 48.58 ± 10.98 in the control group. Setting *α* = 0.05, using the different test, *β* = 0.20. It is calculated by PASS15.0 (NCSS Company, Kaysville, UT) software that 41 participants are needed in each group, with an estimated dropout rate of 20%, 52 patients will be included in each group.

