#### 2.4.2. Inclusion criteria.

Meet the diagnostic criteria of coronary heart disease angina pectoris in traditional Chinese medicine and Western medicine, coronary angiography or coronary angiography showed at least one coronary artery stenosis and catheter stenosis ≥50%.Aged ≥18 years old, and ≤70 years old.Canadian Cardiovascular Society classification of angina pectoris is grade I–III.Angina pectoris attack frequency ≥2 times/week, and ≤6 times/day.Patients agreed to join this study, and signed informed consent.

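### Weekly angina attacks have no assigned analysis rule, and none of the stated rules uses the baseline attack rate or a log-link count model, which costs power if baseline predicts follow-up

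*Protocol article*

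**What the plan says.** Protocol article, section 2.4.2, sets the eligible attack frequency: "Angina pectoris attack frequency ≥2 times/week, and ≤6 times/day". Section 2.7 lists as its third group of outcomes: "Number of angina attacks per week, total amount of nitroglycerin tablets taken during the study". On timing, the same section says: "We will collect the above outcome measures at baseline, at the end of treatment, and at the 6th, 12th and 24th week of follow-up". Weekly attacks are therefore recorded five times, including baseline.

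Section 2.10 gives three rules that might apply:

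- Categorical or count data: "Count and grade data will be expressed as percentage (%), 2-test or non-parametric test". The 2-test is presumably chi-square with a character lost.
- Numerical data: "normal distribution will be analyzed by *t*-test, and skewed distribution will be analyzed by non-parametric test".
- Repeated data: "If the data at multiple time points are normal and have homogeneous variance, the analysis of variance will be used, otherwise the generalized estimating equation" is the stated choice of method.

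Weekly attacks are not assigned to any of the three. No rule names a baseline covariate, a count distribution or a link. The article names no primary outcome, and section 2.3 rests the sample size on the "mean and standard deviation of the scores of the left ventricular ejection fraction of patients after 12 weeks of treatment".

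**The concern.** How many attacks a patient has at follow-up may depend heavily on how many that patient had at entry, and the entry criteria allow patients to differ widely. If the comparison ignores the baseline rate, this between-patient spread stays in the error term. A real reduction in attacks is then more likely to be reported as no difference. The baseline values are collected in any case, so using them costs nothing in data.

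The open choice of rule adds to this. A t-test, a rank test, an analysis of variance and several kinds of GEE all fit the wording, and they differ in power for the same effect.

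**Working it through.** **1. Range at entry.** 6 per day × 7 = 42 per week; 42 / 2 = 21. Eligible rates differ up to 21-fold.

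**2. The plan's own figure.** Section 2.3 gives 54.74 ± 11.17 against 48.58 ± 10.98 for ejection fraction. The difference is 6.16 and the pooled SD is √[(11.17² + 10.98²)/2] = 11.08. A one-sided t-test at 0.05 with 80% power needs 41 per group, and 41/(1 − 0.20) = 51.25, rounded up to 52. The figures reproduce, but they concern ejection fraction. For attacks the article gives no SD, effect or correlation, so there is no power figure to reproduce. I take over only the group size; every other input below is an assumption.

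**3. Analytic check.** With correlation ρ between baseline and follow-up, adjustment multiplies the variance by 1 − ρ². If the adjusted test has 80% power at two-sided 0.05, the unadjusted test has power Φ[(1.960 + 0.842)√(1 − ρ²) − 1.960].

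| ρ | 1 − ρ² | Unadjusted power | Loss (points) |
|---|---|---|---|
| 0.3 | 0.91 | 76% | 4 |
| 0.5 | 0.75 | 68% | 12 |
| 0.7 | 0.51 | 52% | 28 |
| 0.8 | 0.36 | 39% | 41 |

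**4. Simulation of weekly counts.** Assumptions: log-normal patient rates, extra visit-to-visit variation, Poisson counts, observed baseline limited to 2–42, a 40% fall in the control group, true rate ratio 0.70, 41 per group, 600 runs per row. The adjusted model has a log link, treatment, log baseline and robust standard errors. Correlation is that of the log counts.

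| Median rate, log-SD, visit SD | Correlation | t-test | Rank test | Adjusted | Gain over t / rank (points) |
|---|---|---|---|---|---|
| 10, 0.9, 0.4 | 0.57 | 31.8% | 35.2% | 54.0% | 22.2 / 18.8 |
| 8, 0.7, 0.3 | 0.54 | 40.5% | 39.0% | 63.2% | 22.7 / 24.2 |
| 8, 0.7, 0.6 | 0.36 | 29.8% | 31.8% | 39.7% | 9.9 / 7.9 |
| 6, 0.4, 0.4 | 0.23 | 49.3% | 48.2% | 53.2% | 3.9 / 5.0 |
| 8, 0.7, 0.9 | 0.22 | 21.0% | 25.8% | 28.3% | 7.3 / 2.5 |

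With 52 per group the gains run from 31.3 − 28.8 = 2.5 to 75.2 − 51.5 = 23.7 points. A t-test on raw change from baseline does not help here: 11.8% to 27.7% over the five rows, below the t-test on follow-up values in each.

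With no true effect (52 per group, two scenarios), rejection was 5.7–6.0% for the t-test, 5.2–5.7% for the rank test and 7.0% for the adjusted model. The Monte Carlo error is √(0.05 × 0.95/600) = 0.9 points. The smallest gains in the table may partly reflect a slightly liberal robust standard error.

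**5. The GEE option.** A separate simulation (median 7 per week, same fall and rate ratio, 41 per group, 400 runs per scenario) compared versions that the wording allows:

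| Method | Correlation 0.49 | 0.41 | 0.30 |
|---|---|---|---|
| t-test | 38% | 42% | 27% |
| Rank test | 37% | 41% | 34% |
| GEE, identity link, group main effect | 34% | 43% | 34% |
| GEE, identity link, group-by-time contrast at 12 weeks | 22% | 25% | 15% |
| GEE, log link, same contrast | 45% | 49% | 32% |
| Log-link model with log baseline | 54% | 54% | 35% |

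A further run under similar assumptions gave the log-link GEE 30–47% from baseline and end of treatment alone, and 48–67% from all visits if the effect persists. The baseline-adjusted single-visit model had 35–52%, and the t and rank tests 23–41%. Null rejection for the GEE was 6–8%.

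**The case against.** The strongest reply is that the rule for repeated data most plausibly governs this outcome. Attacks are recorded at five visits and are likely to be skewed, so the text points to GEE. A GEE can carry a log link and has baseline among its visits. With all visits and a lasting effect it recovers the loss, as step 5 shows. That stands as a possibility. But the article fixes neither the link nor the contrast, the effect may not last through follow-up, and other versions that the same sentence allows do no better than the rank test.

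A second reply is that link, distribution and covariates belong in an analysis plan, which is not shown. That stands as far as mere absence goes. Section 2.10 does, however, state its methods by data type, and none of them as worded uses the baseline rate. The point is an improvement on what is stated.

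Three stronger readings are tempting, and the article does not support them:

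- A reader might infer that attacks will be turned into percentages and tested by chi-square, since they are counts. Percentages with chi-square point to categorical and ordinal data; a weekly number of attacks more naturally falls under the numerical or repeated-data rule.
- A reader might infer from the 21-fold range that much of the power is certainly lost. The range does not fix the correlation, and the loss can be small.
- A reader might treat attacks as the main outcome because the trial concerns angina. No primary outcome is named, the sample size uses ejection fraction, and the Discussion stresses imaging of cardiac function.

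**Conclusion.** The point holds as one of efficiency and clarity. Weekly attacks have no assigned rule, and no stated rule brings in the baseline rate as a covariate or names a log-link count model. Type I error of the stated t and rank tests is not in question.

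In the simulations of step 4, with 41 or 52 per group and a true rate ratio of 0.70, the cost against unadjusted t and rank tests is about 2 to 25 points of power: roughly 2 to 7 points at log-count correlations of 0.2 to 0.3, and about 16 to 24 at 0.54 or more. These figures rest on assumed rates, spread and effect, because the article gives none of them for attacks. If the planned GEE is given a log link and uses all visits, and the effect persists, part or all of the loss is recovered.

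**What to change.** State in section 2.10 that attacks per week are compared in all randomised patients with a log-link count model: negative binomial, or the planned GEE with a log link and robust standard errors. Treatment and log baseline rate enter as covariates. Report the rate ratio at the end of the 12-week treatment period with its 95% CI, and say that this is not the 12-week follow-up visit. Keep the rank test as a sensitivity analysis. If the GEE covers several visits, baseline should be a covariate and not also an outcome visit.

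Use the same approach for nitroglycerin tablets per week, with the weeks covered as offset and a baseline transform that allows zeros, such as log(x + 1).

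The cost is a few sentences, slightly more modelling and reliance on a log-link model. No new data are needed. Given the 7.0% null rejection in step 4, a small-sample correction to the robust standard errors is worth naming as well.

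If the analysis plan already specifies such a model, section 2.10 need only agree with it.

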**Effectiveness observation**					
Cardiac function indexes	√	√	√	√	√
Blood lipid levels	√	√	√	√	√
Number of angina attacks per week	√	√	√	√	√
Total amount of nitroglycerin tablets	√	√	√	√	√

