### 2.5. Study design

Participants will be divided into a treatment group or control group in a 1:1 ratio by a central network-based randomization tool in this study. Independent statisticians will generate random sequences using SAS 9.3 software (SAS Institute, Cary, NC). When the research assistant enters the patient information on the tablet computer, he/she will be assigned a random number and complete the randomization according to the result of the assignment. Before the end of the study, all persons will be blinded to the group assignment, including the researchers and the patient.

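### Section 2.10 lets the observed distribution choose the test, names no baseline covariate and fixes no decisive analysis for week-12 LVEF, so precision available from the scheduled baseline values is not secured

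*Protocol article*

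**What the plan says.** Section 2.10 (Statistical analysis) sets two rules for measurement data. Under the first, normal data get a t-test, while "skewed distribution will be analyzed by non-parametric test". Under the second, data at multiple time points get analysis of variance if they are normal with homogeneous variance, and generalized estimating equations (GEE) otherwise. The section does not say which rule governs which outcome or visit, how skewness is to be judged, or whether the baseline value enters any model.

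Table 1, under Effectiveness observation, ticks "Cardiac function indexes", lipids, weekly angina attacks and nitroglycerin use at baseline and at all four later visits. Section 2.7 (Outcomes) confirms those times.

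Section 2.3 (Sample size) rests on "left ventricular ejection fraction of patients after 12 weeks of treatment", with "54.74 ± 11.17 in the treatment group and 48.58 ± 10.98 in the control group". That is a comparison of raw post-treatment values. It concludes that "41 participants are needed in each group" and, "with an estimated dropout rate of 20%, 52 patients will be included in each group". Section 2.5 allocates patients "in a 1:1 ratio by a central network-based randomization tool".

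**The concern.** Two things are fixed badly here.

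- **The test depends on the data.** A t-test addresses a difference in means; a rank test addresses a shift in ranks. Section 2.3 sizes the trial on a mean difference of 54.74 − 48.58 = 6.16 LVEF points. If the week-12 values look skewed, the analysis no longer tests that quantity, and the article gives no criterion for when this happens. The choice between analysis of variance and GEE is likewise left to the observed data.
- **Baseline is collected but given no stated role as a covariate.** Where baseline and week-12 LVEF are correlated, adjusting for baseline removes part of the residual variance. An unadjusted comparison leaves that variance in.

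At stake is the width of the interval for the treatment effect and, with it, the chance of detecting the planned effect in a trial of 2 × 52 = 104 patients.

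**Working it through.** **Inputs**
- Means 54.74 and 48.58, SDs 11.17 and 10.98 (Section 2.3). Difference δ = 6.16. Pooled SD = √[(11.17² + 10.98²)/2] = 11.075. Standardised effect = 6.16/11.075 = 0.556.
- From Section 2.3: "Setting *α* = 0.05, using the different test, *β* = 0.20". Sidedness is not stated.
- 41 evaluable per group and 20% dropout (Section 2.3).
- Correlation ρ between baseline and week-12 LVEF: not in the article. Assumed, range 0.3 to 0.7.

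**Step 1: reproduce the plan's figure.** The power of a two-sample t-test comes from the noncentral t distribution with 2n − 2 degrees of freedom and noncentrality δ/(SD·√(2/n)).
- One-sided 0.05: 80% is first reached at n = 41 (power 80.3%). This matches the stated 41.
- Two-sided 0.05: 80% is first reached at n = 52 (power 80.2%). This does not match.
- Dropout: 41/0.80 = 51.25, rounded up to 52. This matches.

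**Step 2: unadjusted week-12 t-test, 41 per group, two-sided 0.05.** Standard error = 11.075 × √(2/41) = 2.446. Noncentrality = 6.16/2.446 = 2.518. Power = 70.1%. The 95% CI half-width is 1.990 × 2.446 = 4.87 points.

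**Step 3: ANCOVA with baseline LVEF.** Residual SD = 11.075 × √(1 − ρ²), with 2n − 3 = 79 degrees of freedom. At ρ = 0.5 the residual SD is 11.075 × 0.866 = 9.592, the standard error 2.118, the noncentrality 2.908 and the half-width 1.990 × 2.118 = 4.22.

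**Step 4: the alternative comparator.** If the multiple-time-point rule were carried out as a change-from-baseline contrast, with equal SDs at both visits, the SD would be 11.075 × √[2(1 − ρ)]. At ρ = 0.7 that is 8.579.

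Two-sided power at 41 per group:

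| ρ (assumed) | Raw week-12 t-test | Change from baseline | ANCOVA | ANCOVA 95% half-width |
|---|---|---|---|---|
| 0.3 | 70% | 56% | 74% | 4.64 |
| 0.5 | 70% | 70% | 82% | 4.22 |
| 0.6 | 70% | 79% | 87% | 3.90 |
| 0.7 | 70% | 89% | 94% | 3.48 |

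ANCOVA reaches two-sided 80% from about ρ = 0.46.

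**Step 5: if the test is one-sided.** The same formulas start from 80.3% for the raw t-test and give 83%, 89% and 97% for ANCOVA at ρ = 0.3, 0.5 and 0.7. The gain in precision does not depend on the sidedness.

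**The case against.** Four stronger readings are tempting. The article does not support them.

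- **That baseline is not used, and that t-tests and rank tests are the whole plan.** Section 2.10 goes on to analysis of variance or GEE for data at multiple time points. Every efficacy outcome has five time points including baseline, so that rule could govern all of them, and a model with baseline as one level would use it. The article does not say that baseline enters in this way, so neither use nor non-use is established. For the same reason 70% is the power of one reading of the plan, not its established power. Against a change-from-baseline contrast the gain at ρ = 0.7 is about 4 points, not 24. ANCOVA is still better at every correlation checked.
- **That the trial lacks power.** This holds only for a two-sided test. Sidedness is unstated, and the sample size reproduces one-sided at 80.3%. The mismatch is a separate sample-size question.
- **That chance imbalance biases the result.** Under 1:1 randomisation the unadjusted t-test is unbiased with valid type I error, and its standard error already allows for chance imbalance. The cost is precision. Silence on stratification in a condensed article is not evidence that there is none.
- **That adjustment is sure to restore 80% power.** Two-sided, it does so only from a correlation of about 0.46, which the article does not give; at 0.3 it reaches 74%.

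It could also be said that a separate analysis plan may settle this. But Section 2.10 does state a method, so that method can be judged as written. What stands against it is that every branch is chosen from the data, none names a baseline covariate, and none is made decisive for week-12 LVEF.

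**Conclusion.** The point holds as one about efficiency and pre-specification, not validity. The tests in Section 2.10 are legitimate under randomisation, but the rule for choosing among them lets the tested quantity depend on the data and secures no use of the baseline values already scheduled. Relative to an unadjusted week-12 t-test with 41 evaluable per group at two-sided 0.05, ANCOVA would raise power from 70% to between 74% and 94%, and cut the 95% half-width from 4.87 to between 4.64 and 3.48 points, for correlations from 0.3 to 0.7. The direction of the gain is secure for any non-trivial correlation. Its size rests on three things the article does not fix: the correlation, the sidedness, and whether the repeated-measures branch would bring baseline in. The change should be made, but the design does not fail without it.

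**What to change.** In Section 2.10, name one analysis of week-12 LVEF in advance: an ANCOVA with treatment and baseline LVEF, or the week-12 treatment contrast from a mixed model adjusted for baseline. State that it will be used whatever a normality or variance check shows. Do the same for left ventricular end-diastolic and end-systolic diameters and the lipids. Keep the rank test as a sensitivity analysis. State the sidedness, so that the analysis and Section 2.3 can be read together.

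The cost is wording and minor analysis work. The baseline values are already in Table 1, so no visit, measurement or patient is added.

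### Section 2.10 picks ANOVA or GEE for multi-visit data by a check that ignores within-patient correlation, and does not say which test decides the week-12 LVEF comparison

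*Protocol article*

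**What the plan says.** Section 2.7 and Table 1 give five measurement times for each efficacy outcome: baseline, end of treatment, and weeks 6, 12 and 24 of follow-up. Section 2.6 sets 12 weeks of treatment, so the three follow-up readings come after it ends.

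Section 2.10 assigns a t-test to normally distributed measurements and a non-parametric test to skewed ones. It then adds a rule for repeated readings: if "data at multiple time points are normal and have homogeneous variance, the analysis of variance will be used, otherwise the generalized estimating equation" takes over. It does not say when the t-test applies and when the multi-visit rule does, and it names no visit or contrast. On the population it says: "Statistical evaluation of full analysis set will follow intent-to-treat".

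Section 2.3 sizes the trial on one comparison, the "mean and standard deviation of the scores of the left ventricular ejection fraction of patients after 12 weeks of treatment", taken as "54.74 ± 11.17 in the treatment group and 48.58 ± 10.98 in the control group". It states that "41 participants are needed in each group" and, "with an estimated dropout rate of 20"%, enrols 52 per group.

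**The concern.** The rule has three weaknesses, all of which follow from what it states.

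- **The check is insufficient.** Normality and equal variance are real ANOVA assumptions, but the main difficulty with five readings per patient is their correlation. For tests involving time in a repeated-measures ANOVA, that means sphericity. GEE is reserved for data that fail the check, although its main purpose is to handle correlation, which is present either way. The method is also chosen after looking at the data.
- **The branches may use different patients.** A standard repeated-measures ANOVA needs every visit; GEE accepts partial records. A distributional check could then settle who is analysed and under which missing-data assumption.
- **The deciding comparison is open.** Normal LVEF data qualify for both the t-test and the multi-visit rule. Within an ANOVA, the group main effect and the group-by-time test answer different questions, and neither is an estimate of the week-12 difference.

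At stake are a modest excess of false positives on one reading of the rule, and a choice of test and contrast that remains open until the data are seen.

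**Working it through.** **Inputs.** From section 2.3: means 54.74 and 48.58, SDs 11.17 and 10.98, α 0.05, β 0.20, 41 evaluable and 52 enrolled per group, dropout 20%. From section 2.7: five visits. Correlations and effect patterns over time are not in the document and are assumed below.

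**The plan's own figure.** Difference = 54.74 − 48.58 = 6.16. Pooled SD = √[(11.17² + 10.98²)/2] = 11.08. Standardised effect = 0.556. A two-sample t-test with one-sided α 0.05 and 80% power needs 41 per group, and 41/0.8 = 51.25, rounded up to 52. Both stated figures reproduce. With two-sided α 0.05 the need would be 52 evaluable and 65 enrolled. The article does not state sidedness; that is a separate matter, but it explains why two-sided power at 41 per group is below 80%.

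**1. Does passing the check protect the ANOVA?** Null trials were simulated with 41 per group, five visits, normal data, equal variances and AR(1) correlation (4,000 runs, Monte Carlo standard error about 0.4 points). The uncorrected group-by-time F test at nominal 5% rejected in:

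- 7.0% at correlation 0.5
- 6.8% at 0.8
- 7.1% at 0.9

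If an ordinary ANOVA were run with the readings treated as independent, the variance of a five-reading mean would be understated by the factor 1 + 4ρ under equal correlation. At ρ = 0.5 the factor is 3, and the group test's error is P(|Z| > 1.96/√3) ≈ 26%. At ρ = 0.7 the factor is 3.8, and P(|Z| > 1.96/√3.8) ≈ 31%. These two figures hold only if that analysis is the one run.

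**2. Who is analysed?** Enrolled: 2 × 52 = 104. Complete cases at 20% dropout: 104 × 0.8 = 83.2, about 83. GEE would also use the partial records of the other 21 or so, where they exist.

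**3. What would a five-visit group main effect estimate?** The true difference at baseline is 0, so the average over five visits is:

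- effect fully sustained: 6.16 × 4/5 = 4.93
- effect fading (1, 0.75, 0.5, 0 of full size): 6.16 × 2.25/5 = 2.77
- effect at week 12 only: 6.16 × 1/5 = 1.23

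Even the most favourable pattern is diluted from 6.16 to 4.93.

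**4. What does a named, baseline-adjusted week-12 contrast give?** Two-sided α 0.05, 41 per group, noncentrality = 6.16/[SD × √(2/41)]:

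- plain week-12 t-test, SD 11.08: noncentrality 2.52, power 70%
- adjusted, ρ = 0.5: SD 11.08 × √(1 − 0.25) = 9.59, noncentrality 2.91, power 82%
- adjusted, ρ = 0.7: SD 11.08 × √(1 − 0.49) = 7.91, noncentrality 3.53, power 94%

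Here ρ is the correlation between baseline and week-12 LVEF.

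**The case against.** Since GEE is the named alternative, the authors probably mean a repeated-measures ANOVA. A reader might infer that the plan carries a 26–31% false-positive rate, but nothing in the text says that readings will be treated as independent. On the likelier reading the excess is modest, about 7%, and confined to tests involving time; the group main effect does not depend on sphericity and holds its level at about 5%. A sphericity correction may also sit in the full plan. All of this stands, and it limits the first weakness to an insufficient check.

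A reader might also infer that the intention-to-treat analysis turns into a completers analysis. The article states no listwise deletion, and missing-data handling is commonly left to a statistical analysis plan that is not shown here. The 83 complete cases also roughly match the planned 2 × 41 = 82 evaluable patients. What stands is narrower: the two branches, as usually run, use different patients under different assumptions.

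Nor can it be said that the rule simply loses power. If the effect fades (6.16, 4, 2, 0), the group-by-time test has about 68–91% power at correlations 0.5–0.7. If the effect is sustained, the group main effect has about 63–74%. The plain week-12 t-test has 70%. Power therefore depends on which test is meant, which the text leaves open.

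Finally, the t-test in the same section could supply the week-12 comparison. It could, but the text does not give it that role.

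**Conclusion.** The point holds as a flaw in a rule that section 2.10 actually fixes, not as a complaint about missing detail. The method for repeated continuous outcomes hangs on a data-dependent check that leaves out within-patient correlation, its two branches can analyse different patients, and no test or contrast is tied to the week-12 LVEF difference behind the sample size.

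The sizes are about 7% instead of 5% for the uncorrected group-by-time test (AR(1) assumed); about 83 of 104 patients in a complete-case ANOVA (planned dropout, no other missed visits); and a diluted target if a five-visit main effect is used. The gain from about 70% to 82–94% power comes from baseline adjustment at assumed correlations of 0.5–0.7, not from dropping the pretest as such. It would be worthwhile to change this before the analysis; it does not invalidate the trial.

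**What to change.** In section 2.10, replace the ANOVA-or-GEE rule for continuous outcomes with one prespecified linear mixed model for repeated measures:

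- include all randomised patients with a post-baseline value;
- fit baseline value, treatment, visit and treatment-by-visit;
- use a covariance structure that models within-patient correlation (unstructured is one option);
- make the end-of-treatment (week-12) treatment contrast the test, and report the follow-up visits as secondary contrasts from the same model.

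This uses incomplete patients under missing at random, a weaker condition than unweighted GEE needs. Log transformation of skewed lipids within the model is optional. The cost is a few sentences: the procedure (MIXED) is in SPSS, the software already named, and no new data or visits are needed.

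### No primary outcome, time point or main analysis set is designated, although the trial is sized on LVEF after 12 weeks, so the false-positive rate of the efficacy conclusion is not controlled

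*Protocol article*

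**What the plan says.** Protocol article, 2.7 Outcomes, lists three groups of measures:

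- three cardiac measures: "left ventricular end-diastolic diameter, left ventricular end-systolic diameter and left ventricular ejection fraction will be measured" by ultrasound;
- four lipids: "total cholesterol; triacylglycerol; low-density lipoprotein cholesterol and high-density lipoprotein cholesterol";
- two symptom measures: "Number of angina attacks per week, total amount of nitroglycerin tablets taken during the study".

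None is called primary or secondary. The section continues: "We will collect the above outcome measures at baseline, at the end of treatment, and at the 6th, 12th and 24th week of follow-up". Table 1 repeats that schedule for all of them.

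Section 2.10 states: "Outcome measure data will be statistically analyzed by the full analysis set and per-protocol set". It does not say which set is the main one. Single comparisons use a t-test or a non-parametric test. Data at several time points go to analysis of variance or, if its conditions fail, to generalized estimating equations. One threshold closes the section: "The difference will be considered statistically significant when" P is below .05. No sidedness, test order or adjustment is given.

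Section 2.3 is the only place that picks out a comparison: "The estimation of sample size is based on the mean and standard deviation of the scores of the left ventricular ejection fraction" after 12 weeks of treatment.

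**The concern.** The trial is presented as confirmatory. The Discussion part of the abstract says the results will settle whether the effect of the granules is a placebo effect. A trial with that aim needs to say which comparison answers the question. Here the comparison that sets the sample size is not tied to the comparison that decides efficacy. If LVEF at 12 weeks showed nothing, the text would not stop a lipid, an angina count, a later visit or the per-protocol result from being put forward instead. The error rate of the efficacy conclusion would then be unknown and above the nominal level, and the sample size would belong to a comparison that need not carry the claim.

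**Working it through.** **Step 1: the plan's own figure (2.3).** Inputs: means 54.74 and 48.58, SDs 11.17 and 10.98, α = 0.05, β = 0.20, 20% dropout.

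- Difference: 54.74 − 48.58 = 6.16. Pooled SD: √((11.17² + 10.98²)/2) = 11.075.
- Normal approximation, n per group = 2(z_α + z_β)²(SD/difference)². One-sided: 2(1.645 + 0.842)²(11.075/6.16)² ≈ 40. Two-sided: 2(1.960 + 0.842)²(11.075/6.16)² ≈ 51.
- Exact t-test: 41 one-sided, 52 two-sided.
- Dropout: 41/0.80 = 51.25, so 52. For the two-sided figure, 52/0.80 = 65.

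The stated 41 and 52 are therefore reproduced by a one-sided 5% test. With a two-sided 5% t-test, 41 evaluable per group give 70.1% power.

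**Step 2: the count.** Outcomes: 3 + 4 + 2 = 9 (2.7). Post-baseline times: 4 (2.7, Table 1). Outcome-by-time tests: 9 × 4 = 36 per set. Sets: 2 (2.10). Because 2.10 allows for a joint analysis over time, nine tests per set is as fair a reading as 36.

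**Step 3: independent tests, no true effect.** Chance of at least one significant result = 1 − (1 − a)^m. Two-sided tests at 5% have a = 0.05 for either direction and a = 0.025 for results favouring the granules.

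- m = 9: 1 − 0.95⁹ = 37.0%; 1 − 0.975⁹ = 20.4%.
- m = 36: 1 − 0.95³⁶ = 84.2%; 1 − 0.975³⁶ = 59.8%.

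**Step 4: correlated tests.** The document gives no correlations, so those below are assumptions. Method: simulated normal test statistics, 40,000 trials per setting, significant if |z| > 1.96; favourable means z > 1.96 with every outcome oriented so that positive is benefit. FAS is the full analysis set and PP the per-protocol set; their test statistics are assumed to correlate 0.95.

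| Tests per set | Outcome r | Time r | FAS, either direction | FAS + PP, either direction | FAS, favourable | FAS + PP, favourable |
|---|---|---|---|---|---|---|
| 9 | 0 | – | 37.2% | 45.4% | 20.3% | 25.6% |
| 9 | 0.3 | – | 32.7% | 40.1% | 16.5% | 20.4% |
| 9 | 0.5 | – | 26.7% | 33.0% | 13.3% | 16.5% |
| 36 | 0.2 | 0.5 | 75.5% | 83.9% | 44.7% | 52.4% |
| 36 | 0.3 | 0.5 | 73.0% | 81.5% | 41.7% | 48.9% |
| 36 | 0.5 | 0.7 | 57.3% | 66.3% | 29.7% | 35.0% |
| 36 | 0.7 | 0.9 | 33.9% | 41.2% | 16.9% | 20.6% |

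The 34-76% band covers outcome correlations from 0.2 to 0.7 and time correlations from 0.5 to 0.9. Weaker correlation lies above it: at outcome r 0 and time r 0.3, the FAS figures are 82.2% and 55.8%.

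**Step 5: the second analysis set.** In the table it adds 3 to 9 percentage points. With outcome r 0.3 and time r 0.5, the either-direction increment is 84.2 − 73.1 = 11.1 points if the sets correlate 0.90 and 78.8 − 72.9 = 5.9 points if they correlate 0.98.

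**Step 6: after naming one comparison.** With one outcome, time and set deciding, the rate is 5% two-sided, or 2.5% in the favourable direction.

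**The case against.** The strongest reply is that a lead outcome exists in all but name. Section 2.3 sizes the trial on LVEF after 12 weeks, cardiac function comes first in 2.7, and the article's Discussion singles out cardiac function by imaging. Test order, multiplicity handling and the role of the per-protocol set are often left to an analysis plan, and the cited registration may already name a primary outcome. This stands in part: the gap is an unlabelled primary, and the absence of an adjustment method alone would be no finding. But imaging covers three measures at four times, and sizing a trial on a measure does not make it the one that decides. The article has full outcome, sample-size and analysis sections, and the rule it does state applies to all outcomes alike.

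Two stronger readings are tempting, and the document supports neither.

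- A reader might infer that a false efficacy result is more likely than not. The rates above 50% mostly count results in either direction, including harm, and assume 36 separate tests. In the FAS, favourable results alone stay at 17-45% over the assumed range; they pass 50% only with weaker correlation or, at the low-correlation end, when the per-protocol set is added. With one test per outcome, even the either-direction rate is at most about 37% in the FAS.
- A reader might infer that the plan accepts any significant cell as proof of efficacy. Section 2.10 says when a difference is called significant; it states no rule for concluding efficacy. The fault is that no such rule is fixed.

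**Conclusion.** The point holds as an unlabelled primary comparison with uncontrolled error. The chance of at least one false-positive result is several times the nominal level on every reading examined. Its exact size cannot be fixed from the document: it depends on assumed correlations and on whether the four times are tested separately or jointly. The per-protocol set is a minor contributor. The favourable-direction figures also assume two-sided testing. If the tests were one-sided at 5%, as the sample size implies, the independent-test rates for a favourable result would be those computed with a = 0.05, namely 37% and 84%. That is one more reason to settle sidedness together with the primary comparison.

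**What to change.** State in 2.7 and 2.10 that LVEF at the end of the 12-week treatment, in the full analysis set, is the primary comparison and alone decides efficacy. Classify all other outcomes and times as secondary or supportive, reported with 95% confidence intervals. Make the per-protocol set a sensitivity analysis. Check that the registration agrees.

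State the sidedness in 2.3 and 2.10. If the test is two-sided at 5%, correct the stated power to about 70% at 41 evaluable per group; keeping 80% would need 52 evaluable, or 65 enrolled, per group.

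Cost: a few sentences before unblinding, with no added patients needed to control the error rate. The real price is that significant secondary results can no longer be claimed as proof of efficacy, and that under two-sided testing the stated power becomes less favourable.
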